## **Methodology**

### **Sample Size**

In order to detect a clinically important difference of 20% in compression depth with a power of 0.8 and a significance level set at 0.05, the sample size calculation yielded a total needed number of participants at 74. Since a drop out rate of approx. 10% must be expected 84 participants will be recruited. Data regarding compression depth utilizing standard CPR techniques in a manikin model ( $43 \pm 12$  mm) were provided by a previous publication and used to estimate the sample size [[name] *et al.* 2013]

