### **Methods:**

After consent of the Research Ethics Board of Medical University of Vienna and obtaining written informed consent of the participants, 84 medically untrained laypersons will be randomised to perform flow-chart assisted CPR for 300s following standard CPR guidelines or CC only CPR. The primary outcome parameter will be the total number of CC achieving the correct depth of 50-60mm. Secondary outcome parameters will be hands-off time, the total number of CC, and the compression rate. The total number of delivered rescue breaths, tidal volume, and time to deliver these will also be evaluated. Furthermore, the subjective point of exhaustion affecting the CPR quality, the reason for discontinuation of CPR if stopped within the 300sec. period and the exhaustion at the end of the CPR measures will be evaluated.

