## Statistical Methods

### Outcome parameters:

The primary outcome is total number of CC achieving the correct depth of 50-60mm in five minutes of manikin CPR. With this the authors want to test the hypothesis that chest compressions are delivered more correctly regarding the depth when utilizing the standard BLS algorithm with the aid of a flowchart as compared to the CC only algorithm utilizing an adapted BLS flowchart in a manikin resuscitation model. The secondary outcome parameter is hands-off time (HOT), which is defined as the sum of total time elapsed during the 300sec. of BLS in which no chest compressions are provided. This includes the pre-compression interval where the initial steps of BLS are performed as well as all interruptions of the CC, e.g. in order to ventilate or pause due to any other reason including exhaustion. Furthermore, the total number of CC, and the compression rate will be evaluated. The total number of delivered rescue breaths, tidal volume, and time to deliver these will also be evaluated.

Furthermore, questions regarding following points will be raised: “During CPR and without stopping your actions, please tell us “NOW” when you perceive your fatigue is affecting the quality of the life support performed”, “How exhausted are you now (question raised directly after discontinuing the CPR) [McDonald *et al.* 2013] (Lickert Like Scale 1-10). If a participant choses to abort resuscitation attempts the open ended question “Why did you discontinue the resuscitation attempts?” will be raised.

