### Data management and calculations

Data will be described as absolute frequencies and percentages for categorical data and using mean and standard deviations (SD) for normally distributed data. All tests for p-values are two-sided and  $p \leq 0.05$  will be regarded to be statistically significant. Students t-test and chi-square test will be used as appropriate. As it is common practice, results of Likert-like scales will be treated as interval-measures and thereby analysed by using parametric tests [Norman *et al.* 2010, Cariio *et al.* 2008]. Local data management will be done using Microsoft Excel for Mac (Microsoft Corporation, USA) and R for Mac (R Foundation for Statistical Computing, Vienna, Austria) for statistical analysis. [R\_Development\_Core\_Team 2009] Graphics will be created using GraphPad Prism for Mac (GraphPad Software Inc., La Jolla, USA).

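### The 0.8 power is stated for a 20% difference in compression depth in mm, but the primary outcome is a count of compressions within 50-60 mm, for which no power is justified

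*Protocol*

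**What the plan says.** The Sample Size section sets the target "In order to detect a clinically important difference of 20% in compression depth with a power of 0.8" and a significance level of 0.05. Its planning values are described as "Data regarding compression depth utilizing standard CPR techniques in a manikin model", namely 43 ± 12 mm, taken from a previous publication. From these, "the sample size calculation yielded a total needed number of participants at 74", raised to 84 for about 10% dropout.

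Under Outcome parameters, "The primary outcome is total number of CC achieving the correct depth of 50-60mm in five minutes of manikin CPR". The Methods part of the Abstract agrees: "The primary outcome parameter will be the total number of CC achieving the correct depth of 50-60mm". The secondary outcomes are hands-off time, total compressions, compression rate, the ventilation measures and the exhaustion questions. Mean compression depth in mm is not among them.

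On analysis, the Data management and calculations section says "All tests for p-values are two-sided" and "Students t-test and chi-square test will be used as appropriate".

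**The concern.** The variable that was sized and the variable that will be tested differ in kind and in units. One is a depth in mm. The other is a per-participant count of compressions falling in a 10 mm window. Nothing in the protocol converts a 20% difference in depth into a difference in that count.

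Two features stop the power from carrying over.

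- **The count depends on how many compressions are given.** The Background reports that compression-only CPR delivers more compressions in total, while the hypothesis expects standard CPR to do better on depth. The two effects pull the count in opposite directions, and the depth calculation sees only one of them.
- **The count is not monotone in depth.** Compressions deeper than 60 mm score nothing, so pressing deeper can lower the count.

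At stake is how the result is read. A null finding would be reported with a claim of 0.8 power that was never calculated for the primary test. The depth measure to which the claim does belong is not a listed outcome.

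**Working it through.** **Inputs from the protocol:** mean 43 mm, SD 12 mm, difference 20%, power 0.8, alpha 0.05, two-sided t-test, 74 evaluable, 84 recruited. The allocation ratio is not stated; 1:1 is assumed, giving 37 or 42 per arm.

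**Step 1. Reproduce the 74.**

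- Difference: 0.20 × 43 = 8.6 mm. Standardised: 8.6 / 12 = 0.717.
- Normal approximation: n per arm = 2 × (1.960 + 0.842)² × 12² / 8.6² = 30.6, so 31 per arm and 62 in total.
- Noncentral t: 31.55, so 32 per arm and 64 in total.
- At 37 per arm, power for an 8.6 mm difference is 0.86.

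The 74 is not reproduced. It appears if the difference is rounded to 8 mm (36.31, so 37 per arm), but 8 / 43 is 18.6%, not 20%. It also appears with a Wilcoxon test at the minimum relative efficiency of 0.864 (31.55 / 0.864 = 36.5, so 37 per arm). The protocol states neither choice. For depth, the discrepancy is on the safe side.

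Dropout: 74 / 0.9 = 82.2, so 83; recruiting 84 is consistent.

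**Step 2. What the sample size supports for any continuous outcome.** Solving the two-sided t-test at alpha 0.05 and power 0.8 gives a detectable difference of 0.66 SD at 37 per arm and 0.62 SD at 42 per arm. For depth, 0.66 × 12 = 7.9 mm. For the count, the same multiple cannot be turned into compressions, because the protocol gives no SD for it.

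**Step 3. What a true 8.6 mm difference could mean for the count.** Each participant's mean depth is drawn from a normal distribution, single compressions vary around it, those within 50-60 mm are counted, and 37 per arm are compared by t-test. Standard CPR is the deeper arm: 43 v 34.4 mm, or 51.6 v 43 mm. Three inputs are assumptions:

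- within-person SD of 2 to 8 mm;
- 300-400 compressions with standard CPR and 400-450 with compression-only CPR;
- whether the 12 mm is the SD between participants' means or the total SD of depths.

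Power for the count with equal totals:

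| Within-person SD | 12 mm between persons: 43 v 34.4 / 51.6 v 43 | 12 mm total: 43 v 34.4 / 51.6 v 43 |
|---|---|---|
| 3 mm | 0.47 / 0.28 | 0.50 / 0.30 |
| 5 mm | 0.59 / 0.34 | 0.70 / 0.47 |
| 8 mm | 0.71 / 0.43 | 0.94 / 0.85 |

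At a within-person SD of 2 mm, with 12 mm between persons, the values are 0.42 and 0.25.

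With unequal totals and 12 mm between persons, power falls to about 0.05-0.30 (300 v 400 compressions) and about 0.05-0.20 (300 v 450). With 12 mm between persons, simulated power for mean depth is 0.87.

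**The case against.** The strongest reply is that the count's power is unknown, which is not the same as low. That stands. A reader might infer from the mismatch that the trial lacks 0.8 power for its primary test; the protocol does not show this. The simulation rests on within-person SDs and compression totals that the protocol does not give, and on how the 12 mm is read, which it does not specify. At one corner of the range power exceeds 0.8. If compression-only CPR were instead both deeper and more numerous, it would be about 0.73-0.98 with 300 v 450 compressions, and a two-sided test would detect that; but this is the reverse of the stated hypothesis.

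Two other readings also go too far. One is that most participants will score near zero because only about 20% would have a mean depth inside the window under a normal distribution with mean 43 and SD 12 mm. A mean outside the window does not imply that no compressions fall inside it: the share of participants with under 5% of compressions in the window is about 60%, 48% and 32% at within-person SDs of 3, 5 and 8 mm. The other is to judge power against a 20% difference in the count. The protocol sets no such target; its 20% refers to depth.

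None of this supplies the missing justification. The surplus of 74 over 64 adds power for depth and says nothing about the count.

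**Conclusion.** The concern holds as a mismatch, not as proof of low power. The 0.8 belongs to a 20% difference in mean depth; it does not apply to the primary count, and nothing in the protocol supports it there. This follows from the text alone and needs no assumption.

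The size of the gap is uncertain. In the hypothesised direction, power for the count is about 0.05-0.70 if 12 mm is a between-person SD. It rises to about 0.85-0.94 only if 12 mm is a total SD, the within-person SD is 8 mm and both arms give equal numbers of compressions. No single value in this range should be quoted as the trial's power.

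Separately, the 74 is inconsistent with the stated inputs, which need about 64 by two-sided t-test. For depth, 74 gives about 0.86 rather than 0.8.

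**What to change.** Keep 84 participants and revise the Sample Size section:

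1. State that the 0.8 power concerns mean compression depth and not the primary outcome.
2. Correct the 74, or state the choice that produced it.
3. State that 37 evaluable participants per arm give 80% power (two-sided t-test, alpha 0.05) for a difference of 0.66 SD in the primary count, or 0.62 SD if all 42 per arm are evaluable. The second figure is relevant because the protocol plans to replace non-completers.
4. Express that difference in compressions if the earlier dataset yields an SD for the count. If it does not, state an assumed SD and show the range. Do not switch to the percentage of correct compressions for this purpose, since that is a different endpoint.
5. Add mean compression depth in mm, from the electronic manikin record, as a secondary outcome.

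The cost is one rewritten paragraph and one added outcome from data to be recorded anyway. The stated detectable effect for the primary outcome will look less favourable than the present text suggests.

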## Description of study days

Volunteers will be invited to participate in the trial by the study personnel. Recruitment will be conducted at a Training Centre of St. John ambulance, Vienna, Austria, before the starts of the lessons. After giving written informed consent, participants will be randomized using a web based randomization program

([www.random.org](http://www.random.org)) and allocated to perform standard CPR or CC only. The randomization for group allocation will be kept in opaque and sealed envelopes.

The evaluation will be performed with an independent investigator using a computer attached Resusci-Anne Skillreporter by Laerdal-Medical® and the Laerdal Skillreporter Software with Segstat (Version 2.3.0, Laerdal Medical, Stavanger, Norway).

The participants will be asked to perform BLS for five minutes on a manikin. The participants will then be asked to undertake any action they deem necessary to rescue the person simulated by the resuscitation manikin. Participants will not be informed about the underlying hypothesis or the outcome parameters. The room will be prepared to minimise outside interruptions.

Additionally, participants will be instructed to indicate the point in time during CPR when they feel that their fatigue is affecting the quality of the life support performed. ("During CPR and without stopping your actions, please tell us "NOW" when you perceive your fatigue is affecting the quality of the life support performed.)

Participants in both groups will receive one of the charts right at the beginning of the scenario with the information that "this chart will provide information on how to perform CPR" and with the start of the clock further instructions regarding its content. Both groups will not receive any further introduction or support. At the beginning of the scenario, the manikin will be positioned in a supine position on the floor. There will be no clock visible for the participant while performing CPR. An investigator is acting as bystander able to call the emergency medical service or to be sent to look for an automated external defibrillator (which will not be available in the scenario). Nonetheless, the investigator is instructed not to provide any information on how to perform CPR and does not physically take part in the primary check, CC, or mouth-to-mouth ventilations.

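### The stated total of 74 participants does not follow from the protocol's own inputs, which give 64 with the named t-test

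*Protocol*

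**What the plan says.** The Sample Size section of the protocol gives the target as follows: "In order to detect a clinically important difference of 20% in compression depth", "with a power of 0.8 and a significance level set at 0.05". It takes 43 ± 12 mm for compression depth under standard CPR from a previous manikin study and reports that "the sample size calculation yielded a total needed number of participants at 74". It then allows for losses: "Since a drop out rate of approx. 10% must be expected 84 participants will be recruited".

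The section names no test or formula, does not convert the 20% into millimetres and gives no allocation ratio. The section Data management and calculations supplies part of this: "All tests for p-values are two-sided", and "Students t-test and chi-square test will be used as appropriate". The section Description of study days says that participants are "allocated to perform standard CPR or CC only", so there are two arms.

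**The concern.** The protocol prints both the inputs and the result of its calculation, so the result can be checked. With the test that the protocol names, the inputs give a clearly smaller number. Either one input or the method differs from what is written, and the reader cannot tell which.

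What is at stake is the planning claim. The trial says that 74 participants are what 80% power for a 20% difference requires. On the stated figures that is not so, and the power actually bought appears nowhere. This cannot be left to a later analysis plan, because the inputs and the total stand side by side in the protocol and disagree.

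**Working it through.** **Inputs**
- Reference mean 43 mm, SD 12 mm, difference 20%, power 0.8, alpha 0.05: Sample Size.
- Two-sided Student's t-test: Data management and calculations.
- Assumed, because not stated: 1:1 allocation, a common SD in both arms, and 20% taken relative to 43 mm.

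**Attempt to reproduce 74**
1. Difference: 0.20 × 43 = 8.6 mm. Standardised difference: d = 8.6/12 = 0.717.
2. Normal approximation: n per arm = 2 × (1.96 + 0.8416)² × (12/8.6)² = 2 × 7.849 × 1.947 = 30.6, so 31 per arm and 62 in total.
3. Exact two-sample t-test (noncentral t): n = 31.55, so 32 per arm and 64 in total, with power 0.806.
4. Gap: 74 − 64 = 10 participants, and 10/64 = 16%.

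**What 74 and 84 give on the same inputs**
- 37 per arm: power 0.860 for 8.6 mm. The difference detectable at 0.80 power is d = 0.660, that is 0.660 × 12 = 7.92 mm, or 7.92/43 = 18.4%.
- 42 per arm: power 0.901.

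**Dropout step**
- 74/0.9 = 82.2, so 83, or 84 with equal arms. This step is consistent with the text.
- 64/0.9 = 71.1, so 72. Dropout does not explain the gap, because 74 is stated before the allowance.

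**Changing one item at a time (t-test, total N)**

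| Change | Total |
|---|---|
| One-sided test | 50 |
| Power 0.85 | 72 |
| Power 0.90 | 84 |
| Alpha 0.025 | 78 |
| 2:1 allocation | 72 |
| 20% of 50 mm (10 mm) | 48 |
| 43 − 43/1.2 = 7.17 mm | 90 |
| 43/0.8 − 43 = 10.75 mm | 42 |

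None gives 74. The one-sided, power and alpha changes also contradict a stated value.

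**Choices that do give exactly 37 per arm**

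| Choice | n per arm before rounding up |
|---|---|
| Difference rounded to 8 mm, SD 12 | 36.31 |
| Difference 8.6 mm, SD 13 | 36.86 |
| t-test on log depth, ratio 1.2, CV 12/43 | 36.40 |
| Rank test at minimum relative efficiency: 31.55/0.864 | 36.52 |

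The protocol states none of these. The log-scale route uses the printed mean, SD and 20%, but on a scale that the protocol never mentions.

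**The case against.** The strongest objection is that the gap is harmless. On the stated inputs 74 gives more power than claimed and 84 gives more still, so no participant and no analysis changes. That is right, and it limits the point to a correction of the text. It does not make the stated figure correct.

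A second objection is that the recalculation rests on things the protocol leaves open: the difference in millimetres, the base of the 20% and the allocation ratio. These are assumptions, though each is the plain reading. The alternatives tried for the base of the 20% and a 2:1 ratio do not give 74 either.

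A reader might go further and infer that 74 came from a Mann-Whitney calculation, so that the trial was sized for one test and will be analysed with another. The documents do not support this. No rank test appears anywhere in the protocol. The match needs the worst-case efficiency of 0.864; with the efficiency for normal data, 3/π, the rank test needs 34 per arm, 68 in total. Three t-test routes also reach exactly 37 per arm, so the match identifies nothing.

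A reader might also infer from the mismatch that the trial is too small. For mean depth the opposite holds. For the primary outcome nothing can be said from these figures. It is a count: "The primary outcome is total number of CC achieving the correct depth of 50-60mm in five minutes of manikin CPR". The protocol gives no mean or SD for it, so neither 64 nor 74 shows the power for that outcome.

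**Conclusion.** The point holds as a discrepancy between stated inputs and stated result. With 8.6 mm, SD 12 mm, two-sided alpha 0.05, power 0.8 and the named t-test, 64 participants are needed, not 74. At 74 the power for a difference in mean depth is 0.86. This assumes 1:1 allocation, a common SD and a 20% difference measured against 43 mm.

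The origin of 74 is undetermined, and the finding needs no explanation of it. The arithmetic is certain under these assumptions. The consequence is small, because the error is on the safe side and recruitment is unaffected. It should still be corrected, since the sample size cannot be verified as it is written.

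**What to change.** Keep 84. Recover the original calculation and correct the sentence in Sample Size so that the absolute difference in millimetres, the SD, the test, the allocation ratio and the total agree with one another and with the analysis section.

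- If the stated inputs and the t-test stand, say that 64 evaluable participants are required and that 74 give 0.86 power for an 8.6 mm difference in mean depth.
- If another difference, SD or scale was used, state it and give the total that follows.
- In either case, say that this power refers to mean depth and not to the primary count of compressions at 50-60 mm.

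The primary analysis should not be changed to a rank test on this ground. The cost is retrieving the calculation and rewording a sentence or two; recruitment and conduct stay as they are.

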## Statistical Methods

### Outcome parameters:

The primary outcome is total number of CC achieving the correct depth of 50-60mm in five minutes of manikin CPR. With this the authors want to test the hypothesis that chest compressions are delivered more correctly regarding the depth when utilizing the standard BLS algorithm with the aid of a flowchart as compared to the CC only algorithm utilizing an adapted BLS flowchart in a manikin resuscitation model. The secondary outcome parameter is hands-off time (HOT), which is defined as the sum of total time elapsed during the 300sec. of BLS in which no chest compressions are provided. This includes the pre-compression interval where the initial steps of BLS are performed as well as all interruptions of the CC, e.g. in order to ventilate or pause due to any other reason including exhaustion. Furthermore, the total number of CC, and the compression rate will be evaluated. The total number of delivered rescue breaths, tidal volume, and time to deliver these will also be evaluated.

Furthermore, questions regarding following points will be raised: “During CPR and without stopping your actions, please tell us “NOW” when you perceive your fatigue is affecting the quality of the life support performed”, “How exhausted are you now (question raised directly after discontinuing the CPR) [McDonald *et al.* 2013] (Lickert Like Scale 1-10). If a participant choses to abort resuscitation attempts the open ended question “Why did you discontinue the resuscitation attempts?” will be raised.

### Data management and calculations

Data will be described as absolute frequencies and percentages for categorical data and using mean and standard deviations (SD) for normally distributed data. All tests for p-values are two-sided and  $p \leq 0.05$  will be regarded to be statistically significant. Students t-test and chi-square test will be used as appropriate. As it is common practice, results of Likert-like scales will be treated as interval-measures and thereby analysed by using parametric tests [Norman *et al.* 2010, Cariio *et al.* 2008]. Local data management will be done using Microsoft Excel for Mac (Microsoft Corporation, USA) and R for Mac (R Foundation for Statistical Computing, Vienna, Austria) for statistical analysis. [R\_Development\_Core\_Team 2009] Graphics will be created using GraphPad Prism for Mac (GraphPad Software Inc., La Jolla, USA).

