A meta-analysis of three previously conducted trials could demonstrate that a simplification of the algorithm (compression-only dispatcher-assisted bystander CPR) led to a 22% increase in survival-to-hospital discharge [Hüpfel *et al.* 2010]. These findings were so convincing that they found representation in a scientific statement of the AHA regarding pre-arrival instruction by the dispatcher [Lerner *et al.* 2012].

Nonetheless, even when bystanders commence CPR, publications have demonstrated fatigue in both, standard and chest compressions-only CPR [Heidenreich *et al.* 2012, McDonald *et al.* 2013]. Despite the fact that chest compressions-only CPR lead to an increase in total number of delivered chest compressions (CC), the fraction of effective CC (reaching the recommended depth) declines among elderlies with the longer duration of CPR [Heidenreich *et al.* 2012]. Noteworthy, in a publication by McDonald and colleagues, fatigue did not affect the rate of compressions. Nevertheless, the compression depth was affected from the second minute onwards [McDonald *et al.* 2013]

This fact is of clinical relevance since for every 5mm increase in compression depth in out of hospital cardiac arrests, the odds of survival and survival with a functional outcome increase [Vadeboncoeur *et al.* 2014]. Even though the optimal depth remains disputed, the current ERC Guidelines recommend a depth of 50-60mm [Koster *et al.* 2010]. Furthermore, and a depth of >50mm has been shown to be associated with improved outcome as well as functional neurological outcome [Vadeboncoeur *et al.* 2014]. Nevertheless, the optimal depth is not undisputed since contrary to previously published data, a recent publication by Stiell and colleagues identified the peak in survival at 45.6mm, below the currently recommended depth [Stiell *et al.* 2014].

The guidelines also recommend a CC rate of 100-120/min [Koster *et al.* 2010]. This is in line with recently published data indicating that the maximum rate of survival to hospital discharge can be achieved when compressing at 100-120/min [Idris *et al.* 2015]. An increase in CC rate over 120/min can decline the probability of return of spontaneous circulation possibly due to a concordant reduction in compression depth [Monsieurs *et al.* 2012, Stiell *et al.* 2012].

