## **Study Population**

Eligible are all volunteers of  $\geq 18$  years of age of non-medical profession, irrespective of gender. Exclusion criteria are professional medical training (nurses, medical doctors, physiotherapists, ergotherapists, emergency medical technician or equivalent), pregnancy (as by verbal response at the time of recruitment), and parallel participation in a clinical trial, or physical impairment or illness prohibiting physical effort.

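### The only named comparison of means is an unadjusted t-test after unstratified randomisation; pre-specified adjustment for age and sex would be a cheap, probably modest gain in precision

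*Protocol*

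**What the plan says.** - **Test.** Under Data management and calculations: "Students t-test and chi-square test will be used as appropriate". The same section adds "All tests for p-values are two-sided". It names no regression model, analysis of covariance or covariate.
- **Allocation.** Description of study days describes a web-based randomisation program with sealed opaque envelopes. No stratification factor is mentioned.
- **Who may enter.** Study Population admits adults from 18 years with no upper age limit, "irrespective of gender". It excludes "pregnancy (as by verbal response at the time of recruitment") and any impairment or illness that rules out physical effort.
- **What is known about rescuers.** The Background cites a study in which the fraction of effective compressions "declines among elderlies with the longer duration of CPR". It also cites a study in which depth suffered from the second minute, without reference to age.
- **Primary outcome.** Outcome parameters defines it as the number of compressions within 50-60 mm during five minutes.
- **What is recorded.** The protocol describes the steps performed, the electronic compression and ventilation data, and the questions on fatigue, exhaustion and stopping. It does not say that age or sex is recorded as a baseline variable.

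**The concern.** Five minutes of compressions is hard physical work, and the eligible population is broad. If age or sex predicts how many compressions land in the depth window, that variation stays in the error term of a t-test. Stratification does not remove it either. The confidence interval for the arm difference is then wider than it need be, which matters in a trial planned at 84.

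Timing matters as well. An analysis plan written later can adjust only for what was collected, so the baseline items have to be settled before recruitment starts.

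**Working it through.** **Inputs from the protocol (Sample Size).** The target is a "clinically important difference of 20% in compression depth", "with a power of 0.8 and a significance level set at 0.05", with planning data of 43 mm and SD 12 mm. The protocol states that "the sample size calculation yielded a total needed number of participants at 74", raised to 84 for dropout of about 10%. I assume 1:1 allocation, because no ratio is given.

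**Step 1. The plan's own figure.** 20% of 43 mm is 8.6 mm, so d = 8.6/12 = 0.72. With (1.960 + 0.842)² = 7.85, n per arm = 2 × 7.85 × 12²/8.6² = 30.6, so 31 per arm and 62 in total. The t-based calculation gives 64. The stated 74 is not reproduced; a difference of 8 mm with the t calculation would give 74. That is a separate matter. Here it means that, on the stated inputs, unadjusted power is above 80%:

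- 74 analysed: Φ(0.717 × √(74/4) − 1.960) = 86.9%
- 84 analysed: Φ(0.717 × √(84/4) − 1.960) = 90.7%

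**Step 2. Effect of adjustment.** If the covariates explain a share R² of the outcome variance within arms, the standard error is multiplied by √(1 − R²). From an 80% base, power becomes Φ(2.802/√(1 − R²) − 1.960). R² is not in the documents; I take 0 to 0.30 as an assumed range.

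| R² | SE multiplier | 84 are worth 84/(1 − R²) | Power from 80% base | Power at 74, plan's inputs | Power at 84, plan's inputs |
|---|---|---|---|---|---|
| 0 | 1.000 | 84 | 80.0% | 86.9% | 90.7% |
| 0.05 | 0.975 | 88 | 82.0% | 88.5% | 92.1% |
| 0.10 | 0.949 | 93 | 84.0% | 90.1% | 93.3% |
| 0.20 | 0.894 | 105 | 87.9% | 93.1% | 95.7% |
| 0.30 | 0.837 | 120 | 91.8% | 95.8% | 97.5% |

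The gain for R² from 0.10 to 0.30 is 4 to 12 points from an 80% base. On the plan's own inputs it is about 3 to 9 points at 74 and 3 to 7 at 84.

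**Step 3. Cost of two covariates.** The table ignores the price of estimating two coefficients. With N = 74 this multiplies the variance by (74 − 3)/(74 − 2 − 3) = 71/69 = 1.029. Break-even is where (1 − R²) × 1.029 = 1, so R² = 1 − 69/71 = 0.03. At R² = 0.10 the net variance ratio is 0.90 × 1.029 = 0.926, and power from the 80% base is Φ(2.802/√0.926 − 1.960) = 82.9% instead of 84.0%. The cost is therefore about one power point.

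**Step 4. What these figures apply to.** The SD of 12 mm is for compression depth. The primary outcome is a count within a window, for which the protocol gives no mean or SD. The relative effect of R² on the standard error applies to any outcome, but the power figures do not carry over directly to the count.

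**The case against.** The strongest reply is that nothing here is wrong. An unadjusted comparison is valid under randomisation, and its error rate already allows for chance imbalance. Covariates are often left to an analysis plan, and one may exist. All of this stands, which is why the point concerns efficiency only. What remains is that the protocol does name a test, and a better one is available at little cost.

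Three stronger readings are tempting, and the documents do not support them.

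- **Age and sex must be known anyway.** A reader might infer this from the eligibility rules. They need only a check that the volunteer is 18 or over and a verbal answer on pregnancy. Neither requires age or sex to be recorded. The case report form is not shown, so it may or may not carry them.
- **The protocol itself makes age prognostic.** The cited finding is a decline over time within elderly rescuers, not a comparison across ages. It is suggestive for age. No passage links sex, body weight or earlier training to depth.
- **Chance imbalance biases the result.** If half the participants are women (an assumption), a sex difference of 15 percentage points or more between arms of 42 arises in roughly 1 in 6 to 1 in 8 randomisations. The SD of the difference is √(2 × 0.25/42) = 0.109, so the normal approximation gives 0.17; exact models give 0.16 or 0.13. This shows neither bias nor an inflated type I error.

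Two further points limit the likely gain. The window has an upper bound, so a stronger rescuer can lose counts by pressing too deep, and the count also depends on rate and pauses. R² with the count may therefore be lower than with depth. Excluding people with prohibiting impairment also removes some of the variation.

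**Conclusion.** The point holds as a low-cost improvement. The named t-test is valid but gives up precision if age and sex predict the count. The size cannot be fixed from the documents. From an assumed 80% base it is nil at an R² of about 0.03, about 2 points at 0.05, 4 at 0.10, 8 at 0.20 and 12 at 0.30, less roughly one point for the two coefficients. It is smaller if unadjusted power is already near 87 to 91%, as the stated inputs imply.

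This rests on an assumed R², on 1:1 allocation, and on a planning SD for depth standing in for the count. It should not be read as an error, a contradiction or a threat to validity.

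**What to change.** 1. State that age and sex are recorded on the case report form before randomisation.
2. Make the primary comparison a pre-specified linear model of the count on arm, age and sex, reporting the adjusted mean difference with a robust 95% CI. The arm coefficient still targets the difference in mean count that the t-test addresses. The robust standard error avoids relying on equal variances for a bounded count.
3. Keep the unadjusted t-test as a sensitivity analysis.
4. Optionally record body weight and any earlier BLS course. Nothing in the protocol supports them as predictors, so they need not enter the primary model.

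The cost is a sentence or two of analysis text, two form items (four with the optional ones) and two degrees of freedom. The covariates must be fixed before any outcome data are seen.
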